### Data management

At each study visit, data will be recorded in an electronic case report form (eCRF) by the designated representative of the respective participating GP practice. Data entry will be performed as soon as possible after data retrieval and an explanation must be provided for all missing data. After completion of a study visit, a pseudonymized eCRF will be transferred to the study center. Pseudonymization is performed according to a software algorithm to assure that data may only be assigned to personal identity at the level of GP practices. Pseudonymized data of the health economic analysis will be transferred from the study center to the Institute for Applied Quality Promotion and Research in Health Care (Göttingen, Germany) for evaluation. All transferred data will be archived by the study center at the end of the trial. No formal data monitoring committee is planned, since no harms are to be expected by implementation of the UCC intervention. A trial steering group from the study center will meet at regular 2-week intervals to monitor trial conduct and data acquisition. To facilitate day-to-day support for participating GP practices a telephone hotline is provided the study center.

### Statistical methods

#### Sample size

The sample size calculation is based on the primary outcome “time to complete wound healing (“time-to-heal”)”. Assumptions are based on the literature: a healing rate after 12 weeks of 60% is assumed in the standard care (control group) [23] and, based on clinical studies on patient-centered interventions, of 80% [24] in the intervention group. With a significance level of *α* = 0.05, an assumed drop-out rate of 20%, and the assumption of exponentially distributed healing curves, a sample size of *n* = 55 patients per study arm is needed to achieve a power of 80% when applying a log-rank test in the classic two-group comparison. In order to take the cluster structure of the data into account (patients in doctors’ practices), the sample size is further adjusted by a design effect of 1.1, which is calculated from a cluster size of *n* = 3 patients per practice and a conservative intra-cluster correlation coefficient (ICC) of 0.05. This results in a total sample size to be recruited for the study of *n* = 126 patients (*n* = 63 per group) in *n* = 42 practices (*n* = 21 per group). In addition, in order to prevent possible drop-outs or recruitment bottlenecks among the GP practices, the target number of practices to be recruited is increased to *n* = 50 (*n* = 25 per group). This will increase the power in the study, as a larger number of clusters has a positive effect on the design effect. The sample size planning was carried out using PASS software.

#### Statistical analysis

The statistical analysis is carried out using a validated R environment with software version ≥ 4.0. The analysis of the quantitative data is performed according to scientific standards. The description of the baseline data will use appropriate descriptive measures such as mean, standard deviation, minimum, median, interquartile range and maximum for continuous parameters and scores, and using absolute and relative frequencies for categorical data. Homogeneity of the study arms will be evaluated by *t* test and chi-square test as appropriate.

The primary outcome “time to ulcer healing” is analyzed using a Cox proportional hazards regression model (shared frailty model) at a two-sided significance level of *α* = 5%. The variables “group,” “ulcer size,” “duration of VLU,” and “BMI” are included as fixed effects and the variable “practice” as a random effect. The use of this model generally increases the power compared to an ordinary log-rank test. Furthermore, the effect size is given by means of a point estimator (hazard ratio and rate difference at 12 weeks) with an associated 95% confidence interval. Further sensitivity analyses include the consideration of the cluster structure via averaging (per practice) and further regression models.

A non-inferiority analysis will be applied to the cost data, in order to determine whether the costs of care incurred in by the intervention group can be considered as high as or lower than the costs of care incurred in by the control group. The ICER will be calculated on the basis of the costs and effects of the intervention and control group as follows:
$$ \mathrm{ICER}=\frac{\varnothing \mathrm{costs}\ \mathrm{of}\ \mathrm{care}\ \mathrm{intervention}\ \mathrm{group}-\varnothing \mathrm{costs}\ \mathrm{of}\ \mathrm{care}\ \mathrm{control}\ \mathrm{group}}{\varnothing \mathrm{effects}\ \mathrm{intervention}\ \mathrm{group}-\varnothing \mathrm{effects}\ \mathrm{control}\ \mathrm{group}} $$

A formula based on the Fieller’s theorem will be used to determine the 95% confidence interval (CI) of the ICER. Using the 95% CI, the cost-effectiveness of the intervention will be interpreted in light of several realistic cost-effectiveness thresholds. Costs and effects are discounted at a rate of 3% p.a. Moreover, discounting rates of 0% and 5% are applied in a sensitivity analysis. The cost-effectiveness may differ for various subgroups and variables unaffected by the intervention. These should be compared or controlled for statistically. To account for uncertainty in the measured parameters, both deterministic and probabilistic sensitivity analyses will be performed, where variables affecting the cost-effectiveness are randomly drawn from a distribution informed by observed data and academic literature.

The evaluation of further secondary outcomes will be carried out with appropriate descriptive measures and comparisons of the study groups using t-tests for continuous variables and chi-square tests for categorical variables. The corresponding effects are described using point estimators with associated 95% confidence intervals. The relationship between variables is checked using the Spearman correlation coefficient. Wherever appropriate, statistical graphs will be provided to visualize the results. Details of the statistical analysis will be further specified in a statistical analysis plan, which will be completed before database closure.

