### Study population and eligibility criteria

Approximately 800 regional GP practices collaborating with the study center will be approached by information letters. Interested GP practices will be screened for inclusion by investigators from the study center according to eligibility criteria for GP practices shown in Table 1.

**Table 1 Tab1:** Eligibility criteria for GP practices

Inclusion criteria	Exclusion criteria
• At least one medical assistant is routinely involved in chronic wound treatment and care	• No involvement of medical assistants in chronic wound treatment and care
• IT requirements for using the CareCockpit software met	• GP practices with more than 20 VLU patients per year
	• IT requirements for the use of the CareCockpit software not met
	• no declaration of consent given

*VLU* venous leg ulcer

Eligible physicians and medical assistants will be introduced to the trial via an information sheet and telephone contact for informed consent. Included GP practices are intended to recruit patients with at least one florid venous leg ulcer. Screening and review of patient eligibility will be performed by the responsible primary care physicians of included GP practices. Patient eligibility criteria are shown in Table 2.

**Table 2 Tab2:** Eligibility criteria for patients

Inclusion criteria	Exclusion criteria
• Patient with VLU or mixed ulcer of predominantly venous origin	• Florid leg ulceration of other origins
• Ulcer duration ≤ 6 months	• Ulcer duration > 6 months (182 days)
• Age ≥ 18 years	• Ankle Brachial Index of affected lower extremity < 0.5 or ankle artery pressure < 60 mmHg
	• Decompensated heart failure (≥NYHA III)
	• Immobility
	• Age < 18 years
	• No ability to give consent

*VLU* venous leg ulcer

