#### Primary outcome

The primary outcome is the time from baseline to ulcer healing defined as complete re-epithelialization with no scab remaining. In case of multiple ulcers, all venous leg ulcers of both legs must meet the criteria of ulcer healing. Assessment of ulcer healing will be performed during regular visits in treating GP practices. If the criteria for ulcer healing are met according to judgment of treating physicians, pseudonymized photo documentation of the same day will be transferred to the study center. The photo documentation must comprise both legs in front and back view as well as close-ups of all leg ulcers. Two independent and blinded investigators who are qualified GPs will review the photo documentation to assess ulcer healing. In case of dissent, a third blinded investigator will be consulted for settlement. If ulcer healing is verified by two investigators, the date of the photo documentation will be recorded as the date of ulcer healing. If healing cannot be verified, treating physicians are informed and the verification process will be repeated weekly for 4 weeks. If the ulcer healing remains unaccomplished, initiation of the verification process will be repeated upon reassessment of the treating physician.

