#### Secondary outcomes

Baseline parameters and the secondary outcomes are determined at baseline (T0), 3 (T1), and 12 months (T2) after patient inclusion (Table 4).

**Table 4 Tab4:** Secondary outcomes

***Outcome***	***Time of measurement***
Number of patients with complete ulcer healing	T1, T2
Number, size of ulcers [cm^2^]	T0, T1, T2
Ulcer recurrence	T1, T2
Pain according to visual analog scale	T0, T1, T2
Health-related quality of life, assessed using the validated questionnaire (EQ-5D-5L)	T0, T1, T2
Depressiveness according to the validated Patient Health Questionnaire (PHQ-9)	T0, T1, T2
Patient satisfaction and information, assessed using the “Patient Assessment of Chronic Illness Care” (PACIC-5A)	T0, T1, T2
Adherence to venous leg ulcer treatment	T1, T2

T0 = baseline, T1 =3 months after inclusion, T2 = 12 months after inclusion

The number of patients with complete ulcer healing will be assessed according to the criteria defined for the primary outcome. Furthermore, the number and sizes of VLU will be assessed. Wound size is determined by the perpendicular method measuring the greatest length and greatest width in cm in perpendicular axes at time points T0, T1, and T2. Ulcer recurrence is defined as the occurrence of any new venous leg ulcer during the observation time. Pain intensity will be measured using the visual analog scale. To assess health-related quality of life, the validated EQ-5D-5L questionnaire of EuroQol Group will be used. Depressiveness will be assessed using the validated Patient Health Questionnaire (PHQ-9) [18]. The Patient Assessment of Chronic Illness Care (PACIC-5A) is used to survey patient satisfaction and quality of patient education [19]. Adherence to VLU treatment elements is assessed by the patient and by caregivers using a Likert scale of 1–5 (non-adherent to adherent) for attendance of appointments and implementation of caregiver recommendations for local wound treatment, change of wound dressings, and general measures. In order to identify barriers to adherence, a free text field is provided to facilitate an indication of individual problems with therapy elements.

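### The endpoint requires every venous ulcer on both legs to heal, but the primary Cox model leaves out the recorded baseline number of ulcers, so ulcer size adjusts only partly for an imbalance in multi-ulcer patients

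*Protocol article*

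**What the plan says.** The protocol article, Primary outcome, defines the event at patient level: "In case of multiple ulcers, all venous leg ulcers of both legs must meet the criteria of ulcer healing". Patients with several ulcers are eligible. The eligibility section states: "Included GP practices are intended to recruit patients with at least one florid venous leg ulcer", and Table 2 sets no upper limit.

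Under Secondary outcomes, Table 4 lists number and size of ulcers at T0, T1 and T2, and the text adds: "Furthermore, the number and sizes of VLU will be assessed". On measurement it says: "Wound size is determined by the perpendicular method measuring the greatest length and greatest width in cm in perpendicular axes". It does not say how the sizes of several ulcers are combined.

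Under Statistical analysis, the shared frailty Cox model is tested two-sided at 5%. On covariates it says: "The variables “group,” “ulcer size,” “duration of VLU,” and “BMI” are included as fixed effects", with "the variable “practice” as a random effect". Number of ulcers is not listed. The article also announces further regression models as sensitivity analyses, and a statistical analysis plan (SAP) to be completed before database closure.

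**The concern.** With several ulcers, the event time is that of the slowest one. An additional ulcer can delay the event or leave it unchanged, but cannot bring it forward. The number of ulcers at T0 thus bears on the outcome through the endpoint definition itself. It is measured before follow-up starts, yet the model does not use it.

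This matters because of how patients enter the trial. Practices, not patients, are randomized. Intervention practices complete mandatory training before their first inclusion, practices are not blinded, and their own physicians screen for eligibility. Randomization of practices therefore does not guarantee a comparable patient mix. If one arm enrols more multi-ulcer patients, the hazard ratio shifts without any treatment effect, unless the model accounts for it.

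**Working it through.** **Plan's own figures.** The planned hazard ratio is ln(0.2)/ln(0.4) = 1.756. For 80% power at two-sided 5% this needs 99 events (Schoenfeld) or 105 (Freedman). Reading the 20% drop-out as spread over 12 months of follow-up (an assumption), the mean event probability is 0.950. That gives 99/0.950/2 = 52.1 or 105/0.950/2 = 55.2 per arm; a Lakatos log-rank calculation gives 54.0. The stated 55 is reproduced. The design effect is 1 + (3 − 1) × 0.05 = 1.1, and 55 × 1.1 = 60.5, rounded up to 21 × 3 = 63. The sample size rests on an unadjusted log-rank test, so the covariate list does not affect it.

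**Direction.** If each ulcer healed independently with probability 0.6 by 12 weeks, all k ulcers would be healed with probability 0.6^k: 60%, 36% and 22% for k = 1, 2, 3. This is only an illustration. The 60% under Sample size is a patient-level rate, and ulcers in one patient probably heal in a correlated way, which narrows the gaps.

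**Shift in the hazard ratio with no treatment effect.** From the documents: 63 per arm, 12 months of follow-up, 20% drop-out, 60% healing at 12 weeks (used here per ulcer). Assumed: exponential healing of each ulcer, hazard proportional to size^-0.3, log-SD of size 1.0, and the shares of two-ulcer patients shown. The simulation had no frailty term and 1,500 runs. Mean hazard ratio, intervention versus control:

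| Adjustment | 20% vs 40% | 15% vs 45% |
|---|---|---|
| none | 1.11 | 1.17 |
| raw size, largest ulcer | 1.08 | 1.14 |
| raw total area | 1.06 | 1.10 |
| log total area | 1.04 | 1.06 |
| total area plus number | 1.00 | 1.00 |

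A separate set of runs at 20% versus 40%, including correlated healing within patients, gave about 1.12 unadjusted, 1.07–1.10 with raw largest or raw total size, 1.03–1.05 with log total area, and about 1.01 once number was added.

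**Sensitivity to assumptions.** With stronger dependence on size (size^-0.5, log-SD 1.3; 20% versus 40%), log total area alone leaves only 1.01. With an 8-point imbalance, the shift is 3–4% unadjusted and 1–2% with raw total area.

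**Scale.** With about 115 events, the standard error of the log hazard ratio is near 2/√115 = 0.19. A shift to 1.10 is ln 1.10 = 0.095, about half a standard error and 0.095/0.563 = 17% of the planned log hazard ratio (ln 1.756 = 0.563). A shift to 1.03 is 0.030, about 5% of it. At 15% versus 45%, rejection under the null was 11.5% with raw largest size, 9% with raw total area and about 6% once number was added.

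**How likely by chance.** The chance SD of the difference in shares is √(2p(1 − p)/63): 7.1 points at p = 0.2 and 8.9 at p = 0.5, ignoring clustering. A 20-point difference is 2.2 to 2.8 SD, so chance alone rarely produces it. Differential enrolment could.

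**Power in balanced arms.** Log instead of raw total area raised power from 0.895 to 0.903 in the first setting and from 0.83 to 0.88 in the stronger one. Adding number brought nothing beyond size.

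**The case against.** The model already contains ulcer size. If that means total area, it carries much of the information on number, and in some settings log total area removes nearly all of the shift. The 20-point imbalance is assumed, and no passage reports differential recruitment. The documents give neither the share of multi-ulcer patients nor their prognosis. How sizes are combined and transformed is normal SAP content. A fourth covariate, partly redundant with size, might be seen as a matter of preference.

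Most of this stands and limits the point. The definition of size alone could be left to the SAP and is not an error here. The omission of number is different: the protocol names the fixed effects of its primary model, so adding one changes that list and does not merely fill in a detail. Announcing unspecified further regression models as sensitivity analyses does not alter the primary estimate.

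A reader might infer three stronger things that the documents do not support:

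- *A strong prognostic factor goes wholly unadjusted.* Its strength is not documented, and size adjusts for part of it.
- *The test is invalid.* With a comparable patient mix, simulated type I error stayed at 0.050–0.051 with number omitted.
- *Substantial power is lost.* Losses of about 1, 5–6 and 11–15 points appear for assumed healing hazard ratios of 0.7, 0.5 and 0.35 for multiple ulcers, but in a model with no size covariate. They are upper-end figures and do not describe the planned model.

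**Conclusion.** The point holds as a recommended improvement, not as a flaw that invalidates the analysis. The endpoint depends on all ulcers, their number is recorded at T0, and the named covariates leave it out. With size alone, an assumed imbalance of 20% versus 40% two-ulcer patients moves a null hazard ratio to about 1.03–1.10, depending mainly on how size is defined, and to less (1.01) if healing depends strongly on size and log total area is used. Adding number brings it to about 1.01. These figures rest on assumed imbalance, size distribution and size dependence. The open recruitment after allocation makes such an imbalance credible but does not show that it will occur. The case for the change is protection against bias, not power. Adjustment corrects only for this factor, not for unmeasured differences between the patients enrolled in the two arms.

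**What to change.** Before database closure, state the fixed effects of the primary model as: group; log of total ulcer area at T0, summed over all venous ulcers of both legs; number of venous ulcers at T0 (1 versus 2 or more); duration of VLU; and BMI. Practice stays as the random effect.

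The cost is one further parameter against roughly 100–120 expected events. Number and size are already recorded at T0, so no new data are needed, and the sample size is unchanged. If the sponsor treats the added covariate as a protocol modification, the article's own rules call for ethics approval and an updated register entry. Making the choice after seeing outcome data by arm would make the primary model post hoc.

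### The protocol fixes t-tests for continuous secondary outcomes and names no use of the T0 values it collects, which costs precision and leaves chance baseline differences in the result

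*Protocol article*

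**What the plan says.** Under Secondary outcomes, the protocol article sets three visits: "Baseline parameters and the secondary outcomes are determined at baseline (T0), 3 (T1), and 12 months (T2) after patient inclusion". Table 4 lists ulcer number and size, pain, EQ-5D-5L, PHQ-9 and PACIC-5A at all three. One row reads "Pain according to visual analog scale T0, T1, T2", and the text on wound size repeats the schedule: "measuring the greatest length and greatest width in cm in perpendicular axes at time points T0, T1, and T2".

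Under Statistical analysis, the method for these outcomes is stated: "The evaluation of further secondary outcomes will be carried out with appropriate descriptive measures and comparisons of the study groups using t-tests" if the variable is continuous, and chi-square tests if it is categorical. No baseline covariate and no practice effect is named.

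The primary Cox model is treated differently. Group, ulcer size, duration of VLU and BMI "are included as fixed effects and the variable “practice” as a random effect". The mention of further regression models belongs to that primary-outcome paragraph, as a sensitivity analysis. The only stated use of baseline data to compare the arms is a significance test: "Homogeneity of the study arms will be evaluated by" t test and chi-square test.

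The section closes with "Details of the statistical analysis will be further specified in a statistical analysis plan, which will be completed before database closure".

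**The concern.** A two-sample t-test takes no covariate. The T0 measurement is usually a strong predictor of the same patient's later score, and here it is already scheduled. Leaving it out of the model makes the confidence intervals wider than the data require.

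It also lets a baseline difference between arms influence the estimate. Such a difference is plausible by chance, since only 21 to 25 practices per arm are allocated. It could also be systematic. Practices are not blinded, they screen and enrol their own patients, and intervention practices must finish training before their first patient enters. Testing homogeneity at baseline may reveal an imbalance but does not correct it.

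Quality of life is at stake in particular: the Discussion names it, beside healing and resource use, as something the trial will evaluate.

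**Working it through.** **Inputs.** From Sample size: 63 patients per arm, 20% drop-out, 3 patients per practice, ICC 0.05, power 80%. From Statistical analysis: two-sided 5%. The protocol gives no power for the secondary outcomes and no T0/follow-up correlation *r*. I assume *r* = 0.3 to 0.7, equal SDs at T0 and follow-up, and the ICC that the plan states for the primary outcome.

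**Plan's own figures.** Design effect = 1 + (3 − 1) × 0.05 = 1.1. Then 55 × 1.1 = 60.5, so 61, and whole practices of three give 21 × 3 = 63 per arm. Both figures reproduce. Completers: 63 × 0.8 = 50.4, about 50 per arm.

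**Precision of a t-test on follow-up values.** In SD units, the standard error is √(1.1 × 2/50) = 0.210. The detectable difference is (1.960 + 0.842) × 0.210 = 0.59 SD.

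**Relative variances.** Follow-up t-test: 1. Change-score t-test: 2(1 − r). Adjusted for T0: 1 − r². The change score exceeds the adjusted variance by 2(1 − r) − (1 − r²) = (1 − r)², which is positive for every r below 1. Detectable differences are 0.588 times the square root of the variance.

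| r | Variance: follow-up / change / adjusted | Detectable difference (SD): follow-up / change / adjusted | Equivalent patients, 1/(1 − r²) |
|---|---|---|---|
| 0.3 | 1 / 1.40 / 0.91 | 0.59 / 0.70 / 0.56 | 1.10 |
| 0.5 | 1 / 1.00 / 0.75 | 0.59 / 0.59 / 0.51 | 1.33 |
| 0.7 | 1 / 0.60 / 0.51 | 0.59 / 0.46 / 0.42 | 1.96 |

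By the same formula, power for a 0.5 SD difference is 66% with the follow-up t-test and 71% / 79% / 92% with adjustment.

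**Simulation check.** 21 practices of 3 per arm, ICC 0.05, 20% drop-out, true effect 0.5 SD, 4000 runs per setting, r = 0.3 / 0.5 / 0.7:
- follow-up t-test: power 69% to 70%
- change-score t-test: 56% / 69% / 89%
- adjusted for T0: 73% / 80% / 93%

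All three simulated analyses ignored clustering (with no effect they rejected in about 5.4% to 6.1% of runs), so these powers run slightly high. The ordering matches the formula.

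**Baseline imbalance.** The chance baseline difference has SD 0.210, hence a 95% range of ±0.41 SD. Given an observed difference Δ, the follow-up t-test is shifted by rΔ, and the change-score t-test by −(1 − r)Δ. At the edge of the range, the follow-up shift is 0.12 / 0.21 / 0.29 SD. With independent patients and Δ = 0.35 SD, the conditional type I error of the follow-up t-test is 7% / 11% / 15%. With Δ = 0.20 SD it is 5.0% / 4.8% / 3.9%, so the inflation appears only with larger imbalances.

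**Ulcer number and size.** The plan assumes 60% and 80% healed at 12 weeks with exponential curves. At 52 weeks this gives 1 − 0.4^(52/12) = 98% and 1 − 0.2^(52/12) = 99.9%. Healing requires all ulcers closed, so apart from recurrence most values are zero at T1 and nearly all are zero at T2. The variance factors above do not carry over to these two outcomes.

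**The case against.** A reader might infer that the tests compare T1 and T2 values and ignore T0 altogether. The document does not say so. It names the test but not the variable tested, and a t-test on change from T0 fits the sentence. That removes the claim that T0 is unused. It does not rescue the method, because the change score is less efficient than adjustment at every r below 1 and over-corrects an imbalance.

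A reader might also infer that the planned estimates are biased. Under sound randomization they are not: an unadjusted comparison is unbiased on average, and chance imbalance is already in its standard error. What stands is lost precision and bias conditional on the imbalance observed. Selective enrolment by unblinded practices would be a recruitment problem, and adjustment removes only the part of it that T0 captures.

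The gain depends on an assumed correlation. At r = 0.3 it is worth only 10% more patients.

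Finally, covariates for secondary outcomes are commonly left to the SAP, which is not shown. That would answer a complaint that something is missing. Here, however, the protocol has already chosen the test, and an SAP that adjusted for T0 would depart from it. The SAP may already do this, and nothing here shows that it does not.

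**Conclusion.** The point holds as one of efficiency and of robustness to imbalance. The protocol states an inferior method for pain, EQ-5D-5L, PHQ-9 and PACIC-5A when a better one needs only data already scheduled. With 50 completers per arm and design effect 1.1, the detectable difference would fall from 0.59 SD to between 0.56 SD (r = 0.3) and 0.42 SD (r = 0.7). The gain runs from small to equivalent to almost doubling the patients. The range rests on the assumed r and on carrying the primary outcome's ICC over to these outcomes.

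The documents do not support extending the same gain, or the same linear model, to ulcer number and size. The t-test's neglect of clustering by practice is a separate matter and adds no weight here, although the remedy also covers it. The change should be made, but the primary analysis does not depend on it.

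**What to change.** For pain, EQ-5D-5L, PHQ-9 and PACIC-5A, replace the t-test with one linear mixed model over T1 and T2. It should contain group, time, group-by-time and the T0 value, with random effects for practice and patient. Report the adjusted group difference with its 95% CI at each time.

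For PACIC-5A, also show the unadjusted estimate. T0 follows practice training in the intervention arm, so the T0 score may already reflect the intervention.

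Do not apply the linear model to ulcer number and size. If these are compared, use a method suited to zero-heavy data, with the T0 value as covariate.

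The cost is wording, since every variable is already in Table 4. The SAP is due before database closure and can carry the change, recorded as a departure from the published t-test sentence. A formal protocol modification would, under Ethical approval, need committee approval and notice to participants.

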### Randomization

Included GP practices will be allocated in a 1:1 ratio to either intervention or control arm via cluster-randomization with variable block length. Randomization sequence will be generated using SAS software and is only accessible to the responsible study biometrician of the Institute of Medical Biometry, University Hospital Heidelberg, Germany.

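### The further secondary outcomes are to be compared with t-tests and chi-square tests that ignore the randomised practices, so their p-values and 95% confidence intervals are modestly too optimistic

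*Protocol article*

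**What the plan says.** The unit of allocation is the practice (Randomization): "Included GP practices will be allocated in a 1:1 ratio to either intervention or control arm via cluster-randomization with variable block length".

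Two parts of the plan allow for this:

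- Under Sample size, "the sample size is further adjusted by a design effect of 1.1". It is built from 3 "patients per practice and a conservative intra-cluster correlation coefficient (ICC) of 0.05".
- Under Statistical analysis, the covariates of the primary Cox model "are included as fixed effects and the variable “practice” as a random effect".

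The same section handles the further secondary outcomes by descriptive measures and "comparisons of the study groups using t-tests for continuous variables and chi-square tests for categorical variables". It then adds: "The corresponding effects are described using point estimators with associated 95% confidence intervals". No practice term, cluster-robust variance or cluster-level summary is named. The sentence covers the outcomes of Table 4: complete healing at 3 and 12 months, number and size of ulcers, recurrence, pain, EQ-5D-5L, PHQ-9, PACIC-5A and adherence.

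**The concern.** Patients of one practice share the same staff, training and habits of care, so their outcomes tend to be alike. A patient-level t-test or chi-square test counts each patient as a full independent observation. It therefore understates the variance of the difference between arms, rejects a true null hypothesis too often and gives intervals with less than 95% coverage.

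The mismatch is plainest for healing. Complete healing at 3 and 12 months is a secondary outcome judged by the primary-outcome criteria. The same healing events would thus be modelled with a practice effect in the primary analysis and compared without one in the secondary analysis.

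These results have some weight. The Discussion says the trial will help to evaluate quality of life, and that a positive impact on the assessed outcomes may lead to wide implementation in primary care.

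**Working it through.** **Inputs from the article**

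- ICC 0.05, cluster size 3, 55 patients per arm before clustering, 126 patients in 42 practices, target raised to 50 practices (Sample size).
- Two-sided 5% level. This is stated for the primary outcome only; I assume the same level for the secondary outcomes.

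**Step 1: reproduce the plan's figure**

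Design effect DE = 1 + (m − 1) × ICC = 1 + 2 × 0.05 = 1.10. Then 55 × 1.10 = 60.5, rounded up to 61. That needs 21 practices of 3, which is 63 per arm and 126 patients in 42 practices. The plan's figures are reproduced.

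**Step 2: effect of ignoring the clusters**

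The true variance of the difference is DE times the variance that the test uses. Hence:

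- true two-sided error = 2 × [1 − Φ(1.96 / √DE)]
- shortfall in interval width = 1 − 1/√DE

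| Patients per practice | ICC | DE | True error | Coverage of nominal 95% interval | Interval too narrow by |
|---|---|---|---|---|---|
| 2.52 (126/50) | 0.05 | 1.076 | 5.9% | 94.1% | 3.6% |
| 3 | 0.05 | 1.10 | 6.2% | 93.8% | 4.7% |
| 3 | 0.10 (assumed) | 1.20 | 7.4% | 92.6% | 8.7% |
| 3 | 0.20 (assumed) | 1.40 | 9.8% | 90.2% | 15.5% |

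For the second row: √1.10 = 1.049; 1.96 / 1.049 = 1.869; 2 × [1 − Φ(1.869)] = 0.062.

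**Step 3: check by simulation**

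Normal outcomes with no treatment effect were simulated, 100,000 runs per setting.

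| Setting, per arm | ICC | Patient-level t-test | t-test on practice means |
|---|---|---|---|
| 21 practices × 3 | 0 | 5.0% | 5.0% |
| 21 practices × 3 | 0.05 | 6.2% | 5.1% |
| 21 practices × 3 | 0.10 | 7.3% | 5.0% |
| 21 practices × 3 | 0.20 | 9.9% | 5.0% |
| 63 patients, practices of 1 to 5 | 0.05 | 6.4% | 4.9% |

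The simulation agrees with the formula. Unequal recruitment makes the inflation slightly worse, and an analysis by practice means removes it.

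**The case against.** **The details are left to a later statistical analysis plan.** The article does say so, and that leaves time to correct the point before database closure. But the tests are already named. This is a stated method that does not fit the design, not an omitted detail.

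**Clustering is covered by the sensitivity analyses.** The article states: "Further sensitivity analyses include the consideration of the cluster structure via averaging (per practice) and further regression models". That sentence stands in the paragraph on the primary outcome, and nothing extends it to the secondary outcomes.

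**The effect is small and these outcomes are not confirmatory.** This largely stands. No significance level or success criterion is attached to the Table 4 outcomes. At the plan's ICC the inflation is about one percentage point. It is smaller still if the planned 20% drop-out leaves no secondary data, which is an assumption: 126 × 0.8 / 50 ≈ 2.0 per practice gives DE 1.05 and an error of 5.6%; with 42 practices, 2.4 per practice gives 5.8%. Unequal cluster sizes push the other way.

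Some stronger readings are tempting, and the article does not support them:

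- **That the ICC probably exceeds 0.05 for PACIC-5A or adherence.** The article gives no ICC for any secondary outcome, and it describes 0.05, set for the primary outcome, as conservative. Larger values can only be shown as an assumed range.
- **That 5 patients per practice is the case to plan for.** Five is a cap (Recruitment and trial timeline). If every practice reached it, 126 / 5 ≈ 25 practices would suffice, half of the 50 targeted.
- **That the t-test is also too liberal for ulcer size because most ulcers will have healed by 3 months.** Many zeros do not by themselves inflate the error. Simulated independent data with 50 patients per arm, 60 to 80% zeros and assumed log-normal areas gave 2.7 to 4.0%. How best to summarise ulcer area is a separate matter of preference.
- **That the baseline comparisons add to the problem.** The sentence beginning "Homogeneity of the study arms will be evaluated by" also ignores practice, but it yields no inference about the treatment effect.

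**Conclusion.** The point holds, with moderate severity: it should be fixed. The named tests do not match the randomised unit and are inconsistent with how the same plan treats its primary outcome. The direction is certain for any positive ICC.

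At the plan's inputs the size is modest: a true error of about 5.9 to 6.4% in place of 5% if all 126 patients are analysed. Figures of 7.4% and 9.8% depend on assumed ICCs of 0.10 and 0.20.

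A reader might infer that the trial's main result is at risk, or that the plan contradicts one of its own figures. Neither follows. The primary model carries practice as a random effect, and the ICC of 0.05 was set for the primary outcome. The cost comparison and the incremental cost-effectiveness ratio have methods of their own and lie outside the sentence at issue.

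**What to change.** Replace the sentence on the further secondary outcomes so that each comparison accounts for practice, with a matching 95% confidence interval:

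- **Continuous outcomes:** a linear mixed model with a random effect for practice.
- **Binary outcomes:** GEE clustered on practice with a small-sample correction, or a mixed logistic model followed by marginalisation to a risk difference. The mixed logistic model alone gives an odds ratio conditional on practice, so the extra step must be written down.
- **Simpler alternative for both:** practice-level summaries. The plan already names averaging per practice for the primary outcome, and in the simulation above a t-test on practice means held the error at 4.9 to 5.1%.

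The statistical analysis plan should carry the same wording before database closure. The cost is a change of text, a few lines of R and slightly wider intervals: about 4 to 5% wider at an ICC of 0.05 (√1.076 = 1.037, √1.10 = 1.049). No further patients, visits or data are needed.
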